## Abstract

**Background:**

The number of people with diabetes is increasing worldwide, especially in developing South Asian countries. Therefore, preventing diabetes at the early stages has become an important issue. Recent clinical trials, systematic reviews, and meta-analysis have shown that zinc has beneficial effects on glycemic and metabolic control in those with diabetes. The present study is designed to evaluate the effects of zinc supplementation on glycemic control and other metabolic parameters in those with pre-diabetes.

**Methods/design:**

The study will be conducted as a randomized, double-blind, placebo-controlled clinical trial for a period of 12 months at the Faculty of Medicine, University of Colombo, Sri Lanka. The study has been approved by the Ethics Review Committee of Faculty of Medicine, University of Colombo (EC/11/189). A total of 200 adults (age 18–60 years) with pre-diabetes will be recruited for the study. They will be stratified according to age, gender, and body mass index and randomly assigned into the test and placebo groups on a 1:1 ratio. The zinc capsules, each weighing 456 mg, will contain the following ingredients:zinc sulfate monohydrate 55.096 mg (elemental zinc 20 mg), lactose monohydrate 399.504 mg, and stearic acid 1.400 mg. The placebo capsule with the same weight will be comprised of lactose monohydrate 454.600 mg and stearic acid 1.400 mg. The subjects will receive either zinc 20 mg capsules or placebo daily for a period of 12 months. The study drugs will be double blinded to both investigators and subjects. The visits and the evaluations will be done as follows: screening (visit 0), 1 month (visit 1), 3 month (visit 2), 6 month (visit 3), and 12 month (visit 4). The following primary outcome measures will be evaluated:fasting plasma glucose (FPG), post oral glucose tolerance test (OGTT), serum insulin, HbA1c, total/low-density lipoprotein (LDL)/high-density lipoprotein (HDL) cholesterol, triglycerides, serum zinc, and appetite using a visual analog scale. Secondary outcome measures include: blood pressure, anthropometry, and dietary assessment using a validated food frequency questionnaire. Data will be analyzed using SPSS v16.

**Discussion:**

The present protocol will aim to establish the beneficial effects of zinc supplementation on disease progression in those with pre-diabetes and also establish its effectiveness in the prevention of diabetes mellitus.

**Trial registration:**

Sri Lanka Clinical Trial Registry: SLCTR/2012/010

## Background

The prevalence of diabetes and pre-diabetes is increasing worldwide because of population growth, aging, urbanization, and increasing prevalence of obesity and physical inactivity. The South Asian region is currently experiencing an epidemic of diabetes and its associated complications [1,2]. The projected increase in prevalence of diabetes is out of proportion to the estimated increase in population [3]. In 1990, the prevalence of diabetes in Sri Lanka was 2.5%; however, most recent studies show more than 1/5 of Sri Lankan adults are dysglycemic [4,5]. The prevalence of diabetes and pre-diabetes in the Sri Lankan adult population in 2005–2006 was 10.3% and 11.5% respectively [5]. Studies from developed countries have shown that the direct cost involved in the treatment of diabetes and its associated complications are high [6]. Furthermore the indirect costs due to early mortality, morbidity, and loss of productivity are likely to be much higher. This is even more pronounced in developing countries of the South Asian region, which are faced with the highest burden of disease [1]. Therefore, simple and effective preventive measures for those at risk of developing diabetes are a timely requirement.

Insulin is stored in β-cells of the pancreas in granules that contains a variable number of zinc atoms. Studies have shown that zinc plays an important role in insulin synthesis, storage, secretion, and action, while also being involved in various stages of carbohydrate and protein metabolism [7,8]. Oxidative stress plays an important role in the pathogenesis of diabetes and its complications. Impaired synthesis of antioxidant enzymes, such as superoxide dismutase and glutathione peroxidase, may be associated with increased oxidative stress [9]. Zinc is an integral structural component of these antioxidant enzymes, and zinc deficiency may impair their synthesis. *In-vitro* studies in animal models and in humans have demonstrated that zinc supplementation improves glycemic control and other metabolic parameters in diabetes [10-13]. A recent systematic review and meta-analysis on the effects of zinc supplementation in patients with diabetes showed that zinc supplementation reduces blood glucose, total cholesterol, and LDL cholesterol while improving glycemic control as demonstrated by a reduction in HbA1c [14]. Zinc supplementation has also shown beneficial effects on insulin resistance and components of the metabolic syndrome in pre-pubertal obese children [15]. However, at present there are no studies evaluating the long-term effects of zinc supplementation in prevention of disease in those at risk of diabetes. The present study aims to evaluate the effects of zinc supplementation on the progression of disease in patients with pre-diabetes from Sri Lanka and determine the metabolic effects of zinc supplementation on glycemic control. In addition, we also aim to evaluate effect of zinc supplementation on body weight and appetite in those with pre-diabetes.

## Methods/design

### Objectives and hypothesis

Objectives: The study aims to evaluate the effects of zinc supplementation on the progression of disease in patients with pre-diabetes from Sri Lanka and determine the metabolic effects of zinc supplementation on glycemic control. Furthermore, we aim to evaluate the effects of zinc supplementation on appetite and body weight in patients with pre-diabetes.

Hypothesis: The glucose concentration of pre-diabetic patients who are treated with elemental zinc 20 mg daily will be lower than that of the control group. We also hypothesize that other diabetes-related metabolic parameters (serum insulin, total cholesterol, triglyceride, HDL cholesterol, LDL cholesterol, and blood pressure) will be improved in the treatment group in comparison to the control group.

### Study design

The study will be conducted as a randomized, double-blind, placebo-controlled clinical trial for a period of 12 months to assess the efficacy of daily zinc 20 mg supplementation in pre-diabetes. The study will be conducted at the Faculty of Medicine, University of Colombo, Sri Lanka. Figure 1 provides an overview of the study.

**Figure 1 F1:**
[figure not shown]
Schematic representation of study design.

### Sample size

The number of patients required for determination of a 20% reduction of fasting plasma glucose in the treatment arm in comparison with the placebo arm at 90% power and 95% confidence interval with a dropout rate of 30% is 100 patients per arm. Hence, a total of 200 subjects with pre-diabetes will be recruited for the study.

### Population

Pre-diabetes is defined as the presence of fasting plasma glucose levels between 110–125 mg/dl or 2-hpost-oral glucose plasma glucose levels between 140–199 mg/dl or both [World Health Organisation (WHO) 2006 criteria] [16]. Study participants will be recruited for the study after obtaining informed written consent.

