### Inclusion and exclusion criteria

#### Inclusion criteria

•Both genders between the ages of 18–60 years, eligible for study through a screening test confirming the presence of pre-diabetes as defined above.

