### Randomization

Subjects will be stratified according to age, gender, and body mass index and randomly assigned into the test and placebo groups at a 1:1 ratio according to the ‘random number table’ generated by SPSS v16.0 software package (SPSS Inc., Chicago, IL, USA).

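### The trial is sized on a relative fall in fasting glucose but also admits people on 2-h glucose alone, so the FPG models should adjust for the visit 0 value and a secondary analysis should show the effect by it

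*Protocol article*

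**What the plan says.** **Who enters.** Population (Protocol article) defines pre-diabetes as "fasting plasma glucose levels between 110–125 mg/dl or 2-hpost-oral glucose plasma glucose levels between 140–199 mg/dl or both". Inclusion criteria makes this the entry rule: "eligible for study through a screening test confirming the presence of pre-diabetes as defined above". No minimum FPG is set for someone who qualifies on 2-h glucose, and no limit is set on how many may do so.

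**What the trial is sized on.** Sample size uses a "20% reduction of fasting plasma glucose in the treatment arm in comparison with the placebo arm", "at 90% power and 95% confidence interval", and concludes that the number needed "with a dropout rate of 30% is 100 patients per arm". The target is applied to all 200 participants.

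**Allocation.** Randomization states: "Subjects will be stratified according to age, gender, and body mass index". The qualifying glucose test is not a stratum.

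**Outcomes and analysis.** Outcomes lists FPG, OGTT and HbA1c together as primary and fixes the contrast for primary outcomes as the change between visit 0 and visit 4. Study period and Table 2 show that visit 0 is the screening visit and that FPG and OGTT are measured in everyone at every visit. Statistical analysis specifies multilevel regression for each outcome. It mentions further covariates only as an example of a sensitivity analysis and refers to a pre-specified analysis plan, which is not shown.

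**The concern.** Two stated choices do not fit together closely. The one quantified target is a proportional fall in FPG, but the entry rule lets in people whose FPG is below the protocol's own 110 mg/dl threshold. For someone who enters at 110–125 mg/dl, a 20% fall means reaching 88–100 mg/dl. For someone who enters on 2-h glucose with an FPG of, say, 95 mg/dl (an assumed value), it means 76 mg/dl. The same proportional response may or may not occur in both groups.

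If it does not, the pooled FPG effect averages over two different effects. A null pooled FPG result would then be harder to interpret, because it could reflect no effect or an effect confined to people with raised FPG.

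A second consequence does not depend on differential response. The visit 0 glucose values both select participants and serve as their baseline. People selected for a high value on a test tend to move back toward the mean on that test. Entry route and visit 0 level therefore predict the change from visit 0 in either arm, and leaving them out of the model gives away precision.

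**Working it through.** **1. The plan's own figure.** With 30% dropout, 100 per arm leaves 100 × 0.70 = 70 evaluable. The article gives neither a mean nor an SD for FPG, so 100 per arm cannot be reproduced forward. Solving backwards, with two-sided 5% (sidedness is not stated) and 90% power:

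SD = δ / [(1.960 + 1.282) × √(2/70)] = δ / 0.548 = 1.83 δ.

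Taking 117.5 mg/dl (midpoint of 110–125) as an assumed mean, δ = 0.20 × 117.5 = 23.5 mg/dl and SD = 42.9 mg/dl. This SD is implied, not stated, and it is large: within a band 15 mg/dl wide the baseline SD cannot exceed 7.5 mg/dl. I therefore use it only as one end of a range.

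**2. Effect retained after pooling.** Let f be the share entering on 2-h glucose alone. Let r be their FPG response relative to that of people with raised FPG. Neither is in the documents.

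Retained fraction = 1 − f + f·r

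| f | r = 0 | r = 0.5 | r = 1 |
|---|---|---|---|
| 0.30 | 0.70 | 0.85 | 1.00 |
| 0.50 | 0.50 | 0.75 | 1.00 |
| 0.70 | 0.30 | 0.65 | 1.00 |

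A 20% fall in everyone is r = 1 on the percentage scale. In mg/dl there is still a small loss, because the 2-h-only group starts lower. With an assumed mean of 95 mg/dl in that group, δ = 0.20 × [117.5(1 − f) + 95f], which is 22.4, 21.3 and 20.1 mg/dl for f = 0.25, 0.50 and 0.75. That is 95%, 90% and 86% of 23.5.

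**3. Power of the pooled FPG comparison**, 70 per arm, δ = 23.5(1 − f) for r = 0:

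| f | δ (mg/dl) | SD 15 | SD 20 | SD 42.9 |
|---|---|---|---|---|
| 0 | 23.5 | >99.9% | >99.9% | 90% |
| 0.25 | 17.6 | >99.9% | 99.9% | 68% |
| 0.50 | 11.8 | 99.6% | 94% | 37% |
| 0.75 | 5.9 | 64% | 41% | 13% |

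With a proportional response instead, power at SD 42.9 is 87%, 83% and 79% for f = 0.25, 0.50 and 0.75. Serious loss of power thus needs a large SD or a high share, together with little or no response in the 2-h-only group.

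**4. Gain from adjusting for the visit 0 value.** With equal variance σ² at both visits and correlation ρ, the change score has variance 2σ²(1 − ρ). After linear adjustment for the visit 0 value the residual variance is σ²(1 − ρ²). The ratio is (1 + ρ)/2. For an assumed ρ of 0.4 to 0.8 this is 0.70 to 0.90, a saving of 30% to 10%. Selection at entry alters the baseline distribution. In an illustrative simulation of the entry rule over the same correlations, the saving for FPG change was about 25% to 7% with continuous visit 0 FPG, and about 14% to 4% with entry category alone. These figures move with the assumed distribution and give an order of magnitude only.

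**5. Precision of an effect by entry category.** If half the sample has raised FPG, 35 per arm remain in that group. Power for δ = 23.5 is then 63% at SD 42.9 and 99.8% at SD 20. For the difference between two equal categories, SE = SD × √(4/35) = 0.338 SD. With r = 0 at SD 42.9 this is 14.5 mg/dl, the ratio 23.5/14.5 is 1.62, and power is about 37%.

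**The case against.** The strongest case against runs as follows. The hypothesis concerns glucose concentration in general, and OGTT and HbA1c are listed as primary beside FPG. OGTT captures the very abnormality on which the 2-h-only group enters, so an FPG null would not be read alone. The sample-size section states a relative effect for everyone with pre-diabetes, and if that holds nothing is lost in relative terms. Baseline adjustment and subgroup estimates are matters that an article commonly leaves to an analysis plan, and one is mentioned. Subgroups would also add to an already long list of primary outcomes.

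Most of this stands, and it rules out four stronger readings that a reader might infer:

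- *That the FPG effect is diluted.* The documents give neither the share nor the response of 2-h-only entrants, so dilution is conditional.
- *That an FPG null could not be told apart from lack of room to improve.* FPG and OGTT are recorded for everyone at visit 0, so the effect can be examined by baseline, and the other glycaemic outcomes help.
- *That the 20% target applies only to people with FPG of 110 mg/dl or more.* The article sets no such limit.
- *That leaving entry route out of the strata is a defect.* Randomization is unbiased without that stratum.

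What the objection does not remove is what the article itself fixes. The primary contrast is change from the visit used for selection, and covariates appear only as a possible sensitivity analysis. Nor does a positive OGTT result explain a null FPG result. An FPG breakdown chosen after seeing a null would carry little weight.

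**Conclusion.** The mismatch between the sizing outcome and the entry rule is real; its effect on the result is conditional. At an assumed 50% share of 2-h-only entrants, the pooled FPG effect would be 50% to 100% of that in people with raised FPG, for a relative response from 0 to 1. Interpretation of a pooled FPG null would be harder to the extent that the response differs. Power suffers badly only under unfavourable combinations: with no response in that half, it is 37% at the SD implied by 100 per arm, but 94% or more at an SD of 15–20 mg/dl.

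The firmer part is that visit 0 level and entry route predict the change from visit 0. Adjusting for them costs nothing in data and should improve precision, by an amount that depends on the unstated correlation between visits. Neither eligibility nor the randomization scheme needs to change.

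**What to change.** Keep eligibility and strata as they are; recruitment has begun.

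1. In the main FPG and 2-h glucose models, adjust for the visit 0 value of that outcome, preferably as a continuous covariate, with or without entry category (raised FPG only, raised 2-h glucose only, both).
2. Pre-specify as a secondary analysis the treatment effect on FPG and on 2-h glucose by visit 0 value or by entry category, through an interaction term, reported beside the all-participant result and labelled exploratory.
3. State that a pooled FPG null will be read together with that analysis and with the OGTT and HbA1c results.

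If the unshown analysis plan already contains items 1 and 2, only a cross-reference is needed. The cost is wording, since Table 2 already schedules both tests at visit 0. It should be settled before unblinding. The downside is that the category-specific estimates will be imprecise, and the absence of a detectable interaction will not show that the effect is the same in all entrants.

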### Inclusion and exclusion criteria

#### Inclusion criteria

•Both genders between the ages of 18–60 years, eligible for study through a screening test confirming the presence of pre-diabetes as defined above.

#### Exclusion criteria

•On any other vitamin or mineral supplementations or the current use of a weight loss medicine or dietary modification.

•History of diabetes mellitus or any metabolic disease.

•Alcohol consumption > 20 g/day.

•Presently having acute diseases or other untreated illness requiring treatment.

•Impaired hepatic or renal functions.

•Lactation, pregnancy or unwillingness to use an effective form of birth control for women of child-bearing years.

•History or presence of any condition, in the investigator’s opinion, that would endanger the individual’s safety or affect the study result.

#### Suspension criteria

•Subject’s demand to discontinue the study.

•Serious adverse events or unusual changes in clinical test results.

•Principal investigator’s decision to terminate the study (low rates of compliance, complications, or unable to sustain the study for various reasons).

### Randomization

Subjects will be stratified according to age, gender, and body mass index and randomly assigned into the test and placebo groups at a 1:1 ratio according to the ‘random number table’ generated by SPSS v16.0 software package (SPSS Inc., Chicago, IL, USA).

### Blinding

The study drugs are double blinded to both investigator and subject. The drug manufacturing will be done by SAP enterprises (PVT) Ltd., Colombo, Sri Lanka, and they will be responsible for the labeling of the zinc capsule and placebo with code numbers.

### Interventions

The treatment drug is a capsule containing elemental zinc 20 mg as the active ingredient; it will have a white-colored body and a cap. The constituents of the zinc capsule are summarized in Table 1. The placebo capsule will contain lactose monohydrate (454.600 mg) and stearic acid (1.400 mg). The placebo will be manufactured to have a similar appearance, shape, weight, taste, and color as thezinc 20 mg capsule. The subjects will receive either one capsule of 20 mg zinc or an identical placebo daily, taken 1 h before breakfast for a period of 12 months.

**Table 1 T1:** Constituents of zinc capsule

	**Specification**	**Quantity per capsule**	**Status**
Zinc sulfate (ZnSO_4_) monohydrate*	USP	55.096 mg	Active ingredient
Lactose monohydrate	BP	399.504 mg	Filler
Stearic acid	USP	1.400 mg	Lubricant
Total weight		456.00 mg	

*Contains 20 mg of elemental zinc.

### Study groups

a. Treatment group: zinc capsule

b. Control group: placebo

### Study period

The study will be conducted for a period of 12 months. The visits and the evaluations will be done as follows: screening (visit 0), 1 month (visit 1), 3 month (visit 2), 6 month (visit 3), and 12 month (visit 4).

### Outcomes

Primary outcome index: The following biochemical assessments will be done at baseline, at the stated intervals, and on completion: FPG, OGTT, serum insulin, HbA1c, total cholesterol, triglycerides, LDL cholesterol, HDL cholesterol, and serum zinc. Furthermore, appetite will be evaluated using the visual analog scale (VAS).

Secondary outcome index:

a. Measurement of systolic (SBP) and diastolic blood pressure (DBP).

b. Anthropometric assessment such as body weight, height, body mass index (BMI), waist circumference (WC), hip circumference (HC), and waist: hip ratio (WHR).

c. Dietary assessment using a validated food frequency questionnaire (FFQ) [17].

The primary and secondary outcomes will be measured at the screening visit (visit 0), 1-month visit (visit 1), 3-month visit (visit 2), 6-month visit (visit 3), and 12-month visit (visit 4). The changes between visit 0 and visit 4 measurements will be analyzed for the primary outcome indexes.

Safety assessment index: The following information will be recorded/measured for the safety assessment: vital signs, general medical examinations, full blood count (FBC), renal function test, liver function test, and adverse events. Liver profile, renal profile, and FBC will be done at the screening day (visit 0), after 6 months (visit 3), and at the end of the study (visit 4). All other assessments will be done at each of the four visits.

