#### Dietary measurements

A culturally validated FFQ will be used to obtain habitual intake of calorie, macro- and micronutrients [17]. A VAS, 10 cm in length with words anchored at each end, expressing the most positive and the most negative rating, will be used to assess hunger, satiety, fullness, and desire to eat.

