### Statistical analysis

Parametric and nonparametric statistical tests will be applied using SPSS version 16 (SPSS Inc., Chicago, IL, USA) and Stata/SE 10.0 (StataCorp., College Station, TX, USA) for the data analysis. For each of the outcomes, multilevel regression analysis will be used to examine differences between trial arms. For binary outcomes the model will be logistic and for continuous outcomes the model will be linear regression. All analyses will follow intention-to-treat principles and a pre-specified analysis plan. Where appropriate, sensitivity analyses will be conducted (for example, control for additional covariates and bootstrapped p values for skewed outcomes). In the case of missing data values, we will apply mean imputation and regression imputation where rates are low and consider multiple imputations where they exceed 10%.

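### Ten outcomes are declared primary with no ranking, although the sample size rests on fasting plasma glucose alone

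*Protocol article*

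**What the plan says.** The Outcomes section of the protocol article puts nine laboratory measures under one primary heading: "FPG, OGTT, serum insulin, HbA1c, total cholesterol, triglycerides, LDL cholesterol, HDL cholesterol, and serum zinc". Appetite on a visual analog scale follows under the same heading, as the tenth. The abstract gives the same set, introduced by "The following primary outcome measures will be evaluated", so the list is not a slip in one place. The Dietary measurements section says the appetite scale "will be used to assess hunger, satiety, fullness, and desire to eat", which is four ratings.

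Outcomes fixes one contrast per measure: "The changes between visit 0 and visit 4 measurements will be analyzed for the primary outcome indexes". The Statistical analysis section adds "For each of the outcomes, multilevel regression analysis will be used to examine differences between trial arms" and "All analyses will follow intention-to-treat principles and a pre-specified analysis plan". That plan is not among the documents at hand.

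Two other sections single out glucose. Sample size uses only FPG: 20% lower on zinc than on placebo, 90% power, 95% confidence, 30% dropout, 100 per arm. Objectives and hypothesis opens with "The glucose concentration of pre-diabetic patients who are treated with elemental zinc 20 mg daily will be lower" and only then turns to insulin, lipids and blood pressure.

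**The concern.** The choice of primary outcomes tells a reader which result decides the trial. Here ten results carry that label, and the article does not say whether one, some or all of them must be positive.

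The list also does not follow from the rest of the article:

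- Nine of the ten primaries have no stated power basis.
- Blood pressure is in the hypothesis but is a secondary outcome. HbA1c, serum zinc and appetite are primary, but the hypothesis paragraph does not name them.
- Appetite and body weight share one further aim, yet appetite is primary and body weight secondary.

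Serum zinc raises a separate problem. The intervention is daily zinc, so serum zinc mainly shows exposure to it. A difference between arms there could be reported as a positive primary outcome and would say nothing about glycaemia or lipids.

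At stake is whether a claim of success on a primary outcome carries the 5% error rate and 90% power that the sample-size statement suggests.

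**Working it through.** **1. Count.** Nine laboratory measures plus appetite give 10 primaries. Without serum zinc, which the supplement may shift by itself and which therefore should not be counted as a true null, there are 9. If each of the four appetite ratings were tested separately, the counts would be 13 with zinc and 12 without. The single contrast (visit 0 to visit 4) means that repeated visits add no further tests.

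**2. The plan's own figure.** The 100 per arm cannot be reproduced, because the article gives neither a standard deviation nor a control mean. It can be turned into a standardised difference. With 30% dropout, completers are 100 × 0.70 = 70 per arm. Reading 95% confidence as two-sided α = 0.05 (an assumption):

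d = √(2/70) × (1.960 + 1.282) = 0.548

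**3. False-positive risk, conditional on a rule.** Suppose each outcome is tested at two-sided 0.05, any one counts as success, and zinc affects none of the k outcomes. Under independence the chance of at least one false positive is 1 − 0.95^k:

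- k = 9: 1 − 0.95^9 = 37.0%
- k = 12: 1 − 0.95^12 = 46.0%

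For a common correlation ρ between the test statistics, with U standard normal:

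1 − E[{Φ((1.96 − √ρ·U)/√(1−ρ)) − Φ((−1.96 − √ρ·U)/√(1−ρ))}^k]

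The article gives no correlations, so ρ is an assumed range.

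| Null outcomes tested | ρ = 0 | ρ = 0.3 | ρ = 0.5 | ρ = 0.7 |
|---|---|---|---|---|
| 9 (appetite once, no zinc) | 37.0% | 32.6% | 26.9% | 20.2% |
| 12 (four appetite ratings, no zinc) | 46.0% | 39.7% | 31.8% | not computed |

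A simulation with a block structure gave 29–34% for 9 outcomes and 37–41% for 12. Its assumed correlations were 0.3–0.7 among glycaemic measures, 0.2–0.4 among lipids, 0.85–0.90 between total and LDL cholesterol, 0.1–0.3 between the glycaemic and lipid groups, and 0.5 among appetite ratings, with appetite unrelated to the laboratory measures.

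**4. Cost of correcting instead.** Bonferroni over ten tests each outcome at 0.05/10 = 0.005, with critical value 2.807. The expected test statistic at 70 completers per arm is 1.960 + 1.282 = 3.242. Power is Φ(3.242 − 2.807) = Φ(0.435) ≈ 66.8%, against the stated 90%. To restore 90%:

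n = 2 × (2.807 + 1.282)² / 0.548² ≈ 112 completers per arm, and 112/0.70 = 160 recruited per arm

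The article plans 100. If nobody dropped out, power at 100 per arm would be 85.7% at 0.005, against 97.2% at 0.05.

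**The case against.** The strongest reply is that the article refers to a pre-specified analysis plan. A testing order or multiplicity rule often sits there, so its absence from a condensed article proves nothing. That stands: a reader might infer that the trial has no error control, and the documents do not support that inference. The point made here does not need it. Which outcomes are primary is protocol content, and the article states it: ten, unranked.

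Second, the percentages depend on a decision rule that the article neither states nor excludes. If all ten outcomes had to be positive, for instance, the false-positive risk would not be inflated at all; power would suffer instead. This also stands. A reader might infer that the trial's false-positive rate simply is 30–50%. The top of that range needs 13 mutually independent null tests, which counts serum zinc as a null, treats four appetite ratings from the same person as unrelated, and takes each as a separate primary test. The article lists appetite only once among the primaries.

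Third, a partial ordering exists: glucose comes first in the hypothesis and FPG sets the sample size. True, but the Outcomes section does not carry it over. The hypothesis also says glucose concentration without choosing between FPG and the oral glucose tolerance test, and participants may enter on the 2-hour value alone. FPG is therefore not the only possible lead outcome. It is the one the trial was sized for.

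Fourth, a reader might infer that serum zinc will almost surely deliver a declared success. The article gives no expected serum response and no hypothesis about serum zinc, so that goes too far. What remains is that an exposure measure is classed as a primary outcome.

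Lastly, Bonferroni is a conservative choice and other corrections would lose less power. The stated sample size nevertheless makes no visible allowance for any correction.

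**Conclusion.** The point holds as a defect in how the primary outcomes are fixed: ten unranked primaries against a sample size and a leading hypothesis that rest on glucose. Confidence is high for that labelling defect.

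The size is conditional. With unadjusted two-sided 0.05 tests and success on any one, the risk among the nine outcomes other than zinc is 37% under independence and about 20–33% for assumed common correlations from 0.7 down to 0.3. It is higher if the four appetite ratings are tested separately. Even the lowest of these is about four times 5%. With Bonferroni over ten, power falls to about 67%, taking the stated 90% as exact at 70 completers per arm.

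The documents do not show which of these would happen, and they do not show that error control is absent from the unseen plan. A single lead outcome matching the sample size would keep both the 5% error rate and the planned power for that outcome.

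**What to change.** Before unblinding, amend the Outcomes section, the abstract's list and the analysis plan as follows:

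- Name the FPG change from visit 0 to visit 4 as the single primary outcome. This uses the measure in Sample size and the contrast already fixed in Outcomes.
- Make the oral glucose tolerance test, HbA1c, insulin, lipids and appetite secondary, either tested in a fixed order or labelled as supportive without adjustment. State whether appetite is one score or four ratings.
- Reclassify serum zinc as an exposure or adherence marker, reported alongside the capsule-count compliance.

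If the analysis plan already holds a testing order, bring the outcome list into line with it. The registry record was not available; if it carries the same list, it needs the same change.

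No measurement, visit or participant is added or dropped, and the trial is still recruiting. The cost is a wording amendment, and the sponsor gives up the claim of several primary outcomes.
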